### Data collection and management

Data are collected electronically using a custom mobile data application (CommCare, Dimagi, Inc, Massachusetts, USA). Data are uploaded daily to a secure, cloud-based server that is password protected and Health Insurance Portability and Accountability Act (HIPAA) compliant. Data are collected on mobile phones that are password protected. All study team members underwent training to learn how to use the mobile devices and data collection application as well as best practices for data collection and confidentiality. Data collection is monitored on an ongoing basis via generation of twice-weekly reports to evaluate study progress, data collection quality, follow-up, and adverse events. Any concerns related to data quality or completeness are discussed with the data collection team, and refresher trainings and supervision visits are completed as needed.

### Sample size

A sample size of 200 caregiver-child dyads was chosen for logistical and resource reasons to provide data for feasibility outcomes and inform the sample size calculation for a future trial [10]. We anticipated we would be able to recruit this number of children who recovered from an episode of SAM during a single malnutrition season based on a previous study that enrolled children with SAM during one malnutrition season and measured the number that recovered [11]. The primary goal of this study is to establish the acceptability, feasibility, and accuracy of caregiver screening, and the trial is not powered for clinically meaningful differences in clinical outcomes.

### Statistical analysis plan

Acceptability and feasibility outcomes will be analyzed descriptively. For clinical outcomes, dichotomous outcomes, including the probability of relapse, we will compare the proportion of children with the outcome by study arm using a Fisher’s exact test. We will compare time to relapse using a log-rank test with a term for randomized treatment assignment. Anthropometric outcomes will be compared by arm with a term for randomized treatment arm and the baseline anthropometric measure, except for growth outcomes (weight gain in g/kg/day and height change in mm/day).

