### Recruitment and eligibility criteria

Caregiver-child dyads are recruited based on nutritional program registers which record outcomes for all children who are treated as part of the outpatient nutritional program. Caregivers of children who have received outpatient treatment for SAM and who have recovered from their SAM episode are screened by a study nurse for eligibility in the present trial. Caregiver-child dyads are eligible to participate if the caregiver is at least 18 years of age, the child is between 6 and 59 months, the child has recovered from an episode of SAM per Burkinabè national guidelines (MUAC ≥ 12.5 cm and/or WHZ ≥ − 2, depending on which criterion the child was admitted to the nutritional program) in the past month, the family is planning to stay in the study area for 6 months to facilitate retention in the study, and with appropriate consent from the caregiver or guardian.

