### Randomization and masking

Caregiver-child dyads are randomized on a 1:1 basis without stratification or blocking. Given the nature of the intervention, investigators, participants, and caregivers are not masked to their assigned treatment. To minimize contamination, each caregiver was given only a single MUAC tape for measuring their child, and multiple children from the same family were not enrolled. Nutrition program staff who evaluate children returning to the clinic for relapse are masked to the intervention assignment.

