### Feasibility and acceptability outcomes

The primary outcomes for the trial are focused on feasibility and acceptability. Feasibility endpoints focus on both the feasibility of conducting a large-scale trial that is powered for relevant clinical outcomes as well as feasibility of integration of caregiver screening into the existing health system. Acceptability focuses on acceptability of integration of caregiver screening from both the caregiver and clinic perspective.*Enrollment and follow-up*. We will assess the speed of enrollment and rate of refusal to enroll in the trial as an indicator of potential for enrollment in a full-scale trial. We will consider success to be enrollment of the target sample size in a 6-month period and refusal of < 10% of eligible participants. We will also assess follow-up at the 6-month primary endpoint visit and consider success to be retention of > 85% of participants at 6 months.Proportion of children who relapse. Assessment of the proportion of children who relapse over the 6-month period post-discharge will establish how frequently children relapse in this population, which will contribute to sample size calculations and justification for a full-scale trial. A low probability of relapse would indicate that interventions intended to reduce the risk of relapse are not warranted.Time to conduct MUAC training. To understand the additional burden on the existing healthcare system for training caregivers to screen for MUAC, the time training takes for each caregiver is measured during the enrollment visit. Extended time for training would be more difficult to implement in real-world nutritional programs. An acceptable time for training will be established via nutrition program interviews as part of the acceptability assessment, described below.*Accuracy of caregiver MUAC training*. At enrollment and 6 months, the accuracy of caregiver MUAC measurements against a gold standard (nutrition program staff) measure is collected. The caregiver and the nutrition program staff member each measure the MUAC of a child attending the clinic masked to each other’s measurements, categorized as “normal” (≥ 12.5 cm, green section of tape), “moderate acute malnutrition” (< 12.5 cm to ≥ 11.5 cm, yellow section of tape), or “severe acute malnutrition” (< 11.5 cm, red section of tape). Due to high levels of caregiver illiteracy, we will not collect numeric measurements. Concordance between color-based categories will be assessed to measure accuracy.*Adherence to the intervention*. Caregivers in the MUAC screening arm will be asked to report how often they screened their child at each follow-up visit. Infrequent caregiver screening would indicate that the intervention may not be acceptable or feasible. Caregivers are also asked to bring back the MUAC tapes at each visit, so the study team can confirm that they are still in possession of the caregiver and ensure that they are not damaged. Missing or damaged MUAC tapes are replaced and recorded.*Adherence to the follow-up schedule*. Standard of care in Burkina Faso includes monthly follow-up visits in the clinic to monitor for signs of relapse. By measuring how often children who have recovered return for scheduled follow-up in the standard of care arm, we aim to understand gaps in care. Low adherence to the follow-up schedule may suggest that additional interventions are needed, or a reduced follow-up schedule should be considered if relapse rates are low.*Caregiver acceptability*. Caregivers complete quantitative surveys related to their experiences screening children for relapse in the screening arm, including data on ease of use, frequency of screening, whether the MUAC tape was lost or stolen, and evaluation of caregiver-perceived importance of screening and whether this is a priority for them in relation to other demands in their lives. A subset of 20 randomly selected caregivers will be invited to participate in an in-depth individual qualitative interview, focusing on their experience with malnutrition screening, diagnosis, treatment, and relapse as well as their child’s general health, and their experiences related to screening. Interviews will be conducted by a study investigator with expertise in qualitative methods. Interviews will be transcribed, translated into English, and analyzed based on an inductive and deductive approach to identify themes guided by immersion crystallization.*Clinic acceptability*. Acceptability from the clinic perspective will be assessed via in-depth interviews with nutritional program staff and clinic leadership. These interviews will focus on the evaluation of MUAC training, ease of implementation, and general barriers perceived by the clinic in the delivery of outpatient treatment for SAM. As part of these interviews, we will evaluate the resources that were required to implement the screening intervention and what is acceptable for implementation from the clinic perspective, including personnel time and space and privacy for training.

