
### Clinical outcomes

In addition to acceptability and feasibility endpoints, a number of clinical endpoints are measured at each follow-up time point. Although the trial is not powered to detect a meaningful difference in clinical endpoints, these data will provide important preliminary data for the design of a full-scale trial should feasibility criteria be met.*Proportion of children relapsing*. The proportion of children who relapse will be compared between study arms. Relapse to SAM will be defined as MUAC < 11.5 cm and/or WHZ < −3. Children who relapse to SAM will be re-admitted to the nutritional program. These children will continue to be monitored in the study. We will also assess the proportion of children who relapse to MAM by arm, defined as MUAC < 12.5 cm and/or WHZ < −2.*Time to detection of relapse*. Time from enrollment to first relapse will be analyzed in both arms. The date of relapse will be defined as the earliest date the relapse was identified in the clinic, via a planned study visit or unscheduled clinic visit.*Anthropometric outcomes*. At all study visits, weight, height, and MUAC measurements will be collected. We will compare growth based on weight and height as well as anthropometric measures defined by weight-for-age *Z*-score (WAZ), height-for-age *Z*-score (HAZ), and WHZ, calculated based on 2006 WHO child growth guidelines [9].*Vital status*. Vital status is assessed at the 6-month visit, and children are classified as alive, died, or unknown. Families who do not return to the clinic for the 6-month study visit will be contacted via phone call and/or home visit to ascertain vital status.*Hospitalization*. At each study visit, caregivers will be asked about any health care sought for the child since their previous visit. Reasons for seeking health care, and if the child was hospitalized overnight, will be recorded. In addition, data from the clinics in which children are enrolled are extracted from clinic records, and hospital records are queried, and data recorded for any hospitalizations of children enrolled in the study. To facilitate linking children to clinic and hospital records, a unique study identification number is placed in each child’s government-issued health card (*carnet de santé*). Clinic and hospital staff are sensitized to record this information for children enrolled in the trial.

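### Weight gain and height change are exempted from baseline adjustment without a stated reason; the comparison stays valid but gives up precision that adjustment could recover at almost no cost

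*Protocol article*

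**What the plan says.** Under Statistical analysis plan, the protocol article states: "Anthropometric outcomes will be compared by arm with a term for randomized treatment arm and the baseline anthropometric measure". The sentence then carves out two outcomes: "except for growth outcomes (weight gain in g/kg/day and height change in mm/day"). The natural reading is that these two are compared by arm with no baseline covariate. No reason is given.

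The covariates exist. Under Clinical outcomes: "At all study visits, weight, height, and MUAC measurements will be collected". The analysis sentence itself presupposes a baseline measure.

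Under Randomization and masking, dyads are "randomized on a 1:1 basis without stratification or blocking". Under Recruitment and eligibility criteria, "the child is between 6 and 59 months", which is a wide span of body size. The sample of 200 dyads was set on logistical grounds, and the article says that the trial is not powered for clinical outcomes.

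**The concern.** Subtracting the baseline value is not the same as adjusting for it. A change score fixes the coefficient of baseline at 1, whereas a model with baseline as a covariate estimates that coefficient. The two are equally efficient only if growth is uncorrelated with baseline size. Over ages 6 to 59 months some correlation is plausible, because younger and smaller children may grow at a different rate from older ones. The documents give no figure for it.

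If there is a correlation, two things follow. The interval for the arm difference is wider than it need be. And since the allocation does nothing to balance age or size, part of any chance imbalance carries into the growth comparison of the trial as run. The article presents its clinical data as preliminary input to a full-scale trial, so the precision of these estimates has some use even though no test on them is powered.

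**Working it through.** The article gives no SD, effect size, correlation or precision figure for growth, so there is no stated figure to reproduce.

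**Inputs from the article.** N = 200, about 100 per arm (Sample size). The retention criterion is above 85% at 6 months (Feasibility and acceptability outcomes), so 0.85 × 200 = 170 analysed, about 85 per arm, if it is only just met.

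**Assumptions.** Two-sided 5% level. r = correlation of the growth outcome with its baseline measure, taken over |r| = 0 to 0.5.

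**Step 1: interval without baseline.** Half-width = 1.96 × √(2/85) = 0.301 SD of the growth outcome.

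**Step 2: interval with baseline.** The variance is multiplied by 1 − r², so the width is multiplied by √(1 − r²). The half-widths below also include the small loss for one estimated coefficient.

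| \|r\| | √(1 − r²) | Half-width with baseline (SD) | Equivalent N, 170/(1 − r²) |
|---|---|---|---|
| 0 | 1.000 | 0.301 | 170 |
| 0.1 | 0.995 | 0.300 | 172 |
| 0.2 | 0.980 | 0.296 | 177 |
| 0.3 | 0.954 | 0.288 | 187 |
| 0.5 | 0.866 | 0.261 | 227 |

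The gain runs from nil to about 13%, and is about 5% at |r| = 0.3.

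**Step 3: chance imbalance.** The 95% range of a baseline difference between arms is ±1.96 × √(2/100) = ±0.28 SD at 100 per arm and ±0.30 SD at 85 per arm. For an imbalance of d SD, the conditional error in the unadjusted comparison is |r| × d, in SDs of the growth outcome. At d = 0.30 this is 0.03 for |r| = 0.1, 0.09 for 0.3 and 0.15 for 0.5.

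**Step 4: validity.** In a simulation of 4,000 trials per setting (170 children, simple randomization, r = 0, −0.1, −0.3, −0.5), both analyses were unbiased on average. Type I error was 0.051 to 0.054 without baseline and 0.050 to 0.058 with it. The mean standard error was 0.154 either way at r = 0. It fell from 0.154 to 0.147 at r = −0.3 and from 0.153 to 0.133 at r = −0.5.

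**Step 5: does a high baseline to 6-month correlation make the gain negligible?** Call that correlation ρ. With equal SDs at both times, the variance ratio is (1 + ρ)/2. At ρ = 0.9 this is 0.95, an interval 2.5% narrower; at ρ = 0.98 it is 0.99, or 0.5% narrower.

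That result depends on the equal SDs. If smaller children grow faster, the spread of height shrinks. Take illustrative values, not from the article: baseline SD 10 cm, follow-up SD 9.5 cm, ρ = 0.98.

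- Covariance = 0.98 × 10 × 9.5 = 93.1.
- Variance of change = 100 + 90.25 − 186.2 = 4.05.
- r = (93.1 − 100)/(10 × √4.05) = −0.34, an interval about 6% narrower.

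With a follow-up SD of 9 cm the same steps give r = −0.55, about 16% narrower. A high ρ alone therefore does not settle the matter.

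**The case against.** The case for leaving the plan as it is has real substance.

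- **The analysis is valid.** Comparing a rate of change between randomized arms is unbiased with correct type I error, and ordinary intervals already allow for chance imbalance. This stands.
- **Subtraction already does part of the work.** A reader might infer that baseline imbalance goes wholly uncorrected. It does not. With equal SDs and ρ = 0.9, the share of an imbalance passing through is 0.9 for the raw 6-month value and 0.9 − 1 = −0.1 for the change. What remains is a residual r × d, here a slight over-correction.
- **The size is assumed.** This stands. Taking |r| up to 0.6 and all 200 dyads as analysed would suggest intervals 20% narrower and an equivalent N of 200/(1 − 0.36) = 312. Nothing in the article supports that correlation, and its retention criterion allows for only about 170 children.
- **The SD for planning.** A reader might infer that the unadjusted SD is too large to plan from. It is the right input for an unadjusted full trial; only an adjusted one needs the residual SD, which the collected data can supply.
- **The Z-scores are already adjusted.** WAZ, HAZ and WHZ draw on the same weights and heights and do get a baseline term. But they are separate outcomes and do not replace weight gain and height change, which the article also plans to compare.
- **Little is at stake.** The primary outcomes are descriptive, and no success criterion depends on a growth contrast. This stands and limits the weight of the point.

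**Conclusion.** The point holds as a minor matter of efficiency, not as an error that invalidates anything. The exception is explicit, unexplained, and forgoes a covariate that is already collected. In large samples, adding baseline to a randomized comparison never loses precision, and it gains whenever growth correlates with baseline. The gain is 0 to about 13% in interval width over an assumed |r| of 0 to 0.5. The residual conditional error is 0.03 to 0.15 SD for a 0.30 SD imbalance at |r| from 0.1 to 0.5. Both ranges rest on an r that the article does not give, on about 85 analysed children per arm, and on a two-sided 5% level. The documents do not support reading this as bias, as type I error inflation, or as a threat to the feasibility conclusions.

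**What to change.** Delete the exception. Compare weight gain (g/kg/day) by randomized arm with baseline weight in the model, and height change (mm/day) by arm with baseline height. Age at enrollment is an optional further covariate; the plan uses it for no other outcome. Keep the unadjusted comparison as a sensitivity analysis, and report both the unadjusted and the residual SD so that planners of the full trial can take whichever matches their analysis. Make the change before outcomes are compared by arm, so that the covariate is not chosen after seeing results. The cost is one sentence in the plan, one degree of freedom (two with age), and no new data.

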### Dissemination plan

Results of the pilot study will be shared with local stakeholders, including clinic leadership, as well as members of the Ministry of Health in Burkina Faso. Results will be presented nationally and internationally via presentations at conferences and publication in peer-reviewed journals.

## Discussion

Children with SAM are at high risk of mortality [12, 13], and interventions for SAM often focus on the acute phase of recovery immediately following admission to the nutritional program. Relapse to SAM or MAM following recovery from an episode of SAM is common, and these children may be at increased risk of mortality and morbidity due to repeated episodes of acute malnutrition [3, 14–17]. However, evidence-based interventions for prevention of relapse and post-discharge mortality are limited [18]. In the current trial, we aim to establish the feasibility and acceptability of training caregivers to screen for relapsed acute malnutrition using standard MUAC tapes. The 2023 WHO guidelines on prevention and management of acute malnutrition include nutritional counseling and education at the time of exit from the nutritional program after recovery [19]. If acceptable, feasible, and effective, inclusion of training in screening for relapse in caregiver screening at the time of exit may be an easily scalable intervention to reduce relapsed wasting in children under 5 years of age.

We anticipate that the current trial will provide critical feasibility data to inform both a full-scale trial and future interventions related to MUAC screening for relapsed SAM. Feasibility data will include both quantitative and qualitative measures of caregiver and clinic experiences with MUAC screening, and these data may inform changes to training or other protocols for MUAC screening interventions to be tested in a full-scale trial. In addition, data will provide critical inputs for sample size calculations. Data collected as part of this feasibility trial will help identify gaps in current post-recovery SAM surveillance, for example, by evaluating adherence to the follow-up protocol. This may lead to the development of new or additional interventions that could be integrated with MUAC screening to improve post-discharge surveillance for children who have recovered from an episode of SAM.

This feasibility trial is designed to provide preliminary evidence supporting larger-scale evaluation of MUAC-based screening interventions for caregivers of children who have recovered from SAM. The study is not powered to detect potentially meaningful clinical differences between children whose caregivers have been randomized to the MUAC screening arm compared to standard of care. In addition, this study does not evaluate a reduced follow-up schedule post-recovery from SAM. Although a reduced follow-up schedule may lead to worse outcomes during the acute phase [7], if MUAC screening with the standard follow-up schedule is feasible, future studies could consider evaluation of a reduced post-recovery follow-up schedule to reduce caregiver burden. Data from this trial would help inform such a study, for example, by establishing caregiver adherence to screening and follow-up. Finally, it is possible that caregivers will share MUAC tapes, which could introduce contamination, further limiting the study’s statistical power. However, we anticipate that the study will yield important data relating to implementation of this intervention, including information on MUAC tape sharing.

Overall, we anticipate that the results of this feasibility study will provide preliminary evidence of the integration of MUAC screening by caregivers into the post-recovery follow-up protocol for children who have recovered from an episode of SAM. This work is expected to support future evaluation of interventions for the prevention of relapse in this population.

### Trial status

The text of this manuscript refers to protocol version 1.4, 18 December 2023. Recruitment began on 1 December 2023 and is ongoing as of 31 January 2024. The trial is expected to continue through September 2024.

## Data Availability

Not applicable (no data reported).

## Abbreviations

SAM: Severe acute malnutrition
MUAC: Mid-upper arm circumference
WHZ: Weight-for-height *Z*-score
RUTF: Ready-to-use therapeutic food
CSPS: Centre de Santé et de Promotion Sociale
HAZ: Height-for-age *Z*-score
WAZ: Weight-for-age *Z*-score
HIPAA: Health Insurance Portability and Accountability Act
WHO: World Health Organization
